# Hyperhydration to Improve Kidney Outcomes in Children with Shiga Toxin-Producing *E. coli* Infection: a multinational embedded cluster crossover randomized trial (the HIKO STEC trial)

**DOI:** 10.1186/s13063-023-07379-w

**Published:** 2023-05-27

**Keywords:** Shiga toxin-producing E. coli (STEC), Hemolytic uremic syndrome (HUS), Hyperhydration, Euvolemia, Children, Gastroenteritis, Bloody diarrhea, Emergency department, Acute kidney injury, Hospitalization

## Abstract

**Background:**

Shiga toxin-producing *E. coli* (STEC) infections affect children and adults worldwide, and treatment remain solely supportive. Up to 15–20% of children infected by high-risk STEC (i.e., *E. coli* that produce Shiga toxin 2) develop hemolytic anemia, thrombocytopenia, and kidney failure (i.e., hemolytic uremic syndrome (HUS)), over half of whom require acute dialysis and 3% die. Although no therapy is widely accepted as being able to prevent the development of HUS and its complications, several observational studies suggest that intravascular volume expansion (hyperhydration) may prevent end organ damage. A randomized trial is needed to confirm or refute this hypothesis.

**Methods:**

We will conduct a pragmatic, embedded, cluster-randomized, crossover trial in 26 pediatric institutions to determine if hyperhydration, compared to conservative fluid management, improves outcomes in 1040 children with high-risk STEC infections. The primary outcome is major adverse kidney events within 30 days (MAKE30), a composite measure that includes death, initiation of new renal replacement therapy, or persistent kidney dysfunction. Secondary outcomes include life-threatening, extrarenal complications, and development of HUS. Pathway eligible children will be treated per institutional allocation to each pathway. In the hyperhydration pathway, all eligible children are hospitalized and administered 200% maintenance balanced crystalloid fluids up to targets of 10% weight gain and 20% reduction in hematocrit. Sites in the conservative fluid management pathway manage children as in- or outpatients, based on clinician preference, with the pathway focused on close laboratory monitoring, and maintenance of euvolemia. Based on historical data, we estimate that 10% of children in our conservative fluid management pathway will experience the primary outcome. With 26 clusters enrolling a mean of 40 patients each with an intraclass correlation coefficient of 0.11, we will have 90% power to detect a 5% absolute risk reduction.

**Discussion:**

HUS is a devastating illness with no treatment options. This pragmatic study will determine if hyperhydration can reduce morbidity associated with HUS in children with high-risk STEC infection.

**Trial registration:**

ClinicalTrials.gov NCT05219110. Registered on February 1, 2022.

## Administrative information

Note: the numbers in curly brackets in this protocol refer to SPIRIT checklist item numbers. The order of the items has been modified to group similar items (see http://www.equator-network.org/reporting-guidelines/spirit-2013-statement-defining-standard-protocol-items-for-clinical-trials/).

## Introduction

### Background and rationale {6a}

Globally, there are over 2.8 million [1] cases of Shiga toxin-producing *E. coli* (STEC) infection each year. In 2012, the Centers for Disease Control and Prevention estimated that 96,534 high-risk ((i.e., Shiga toxin 2-producing (Stx 2)) STEC infections occur yearly in the US [2, 3]. Over 60% of these infections occur in children, half of whom are under 5 years old [2, 4]. Hemolytic uremic syndrome (HUS, the triad of hemolytic anemia, thrombocytopenia, and kidney failure) is the most serious potential complication of STEC infections [5], and, in North America, *E. coli* O157:H7 is the most common cause of this post-diarrheal microangiopathic disorder.

Most STEC-infected children present for care when bloody diarrhea prompts medical attention; 15–20% of children infected with high-risk STEC develop HUS, and this complication ensues a median of ~ 7.5 days following the onset of diarrhea [6]. In recent years, mortality of HUS remains about 3% [7]. Up to half of survivors have chronic kidney disease [8]. HUS is believed to be a consequence of a cascade triggered by brief circulation of Stx early in the illness; thus, to prevent HUS or diminish its severity, interventions early in illness are needed.

Over four decades of research on STEC have produced elegant cellular and pathogen genomic insights but have not generated any interventions to reduce or avoid major complications including acute kidney injury (AKI). Narcotics [9–12], antibiotics [7, 13–15], antimotility agents [9, 10], and non-steroidal anti-inflammatory drugs [14] are either ineffective or predispose to poor outcomes. In the absence of effective treatments, there is evidence of considerable practice variation [16, 17]. A multicenter study showed that 59% of STEC-infected children presenting to pediatric emergency departments were directly hospitalized, but of those managed as outpatients, 17% returned to hospital with HUS [16]. This reflects the wide spectrum of care provided to STEC-infected children with treatments varying from a “wait and see” approach (i.e., children managed at home and instructed to seek care when complications ensue) to “admit all” for high-volume hyperhydration (see below). This variation reflects the lack of evidence to guide care, and the limited awareness of front-line clinicians (i.e., family physicians, pediatricians, emergency physicians) regarding the natural history of STEC infection [17].

Observational studies have shown that early high-volume intravenous fluid administration (hyperhydration) is associated with reduced severity of kidney injury and may be effective in mitigating or preventing complications [18–20]. Even though vascular injury is underway by the time children present with STEC-induced diarrhea [21, 21–23], we hypothesize that there is an opportunity to reduce kidney damage and maintain kidney function through intravascular volume expansion in children who present for care before HUS ensues [24, 25]. This hypothesis is generated from three complementary sets of data: the poor outcomes associated with STEC infections in children who have relative hemoconcentration (and other signs of volume contraction) when they present with HUS, the partial success of aggressive intravenous volume expansion at the point of diagnosis with HUS, and improved outcomes in observational studies where large volumes of isotonic intravenous fluids were administered before the development of HUS.

### Volume contraction when HUS is diagnosed is a risk for poor outcomes [26]

Multiple series of children with diarrhea-associated HUS demonstrate that hemoconcentration and/or dehydration at admission (i.e., when HUS is diagnosed) have worse outcomes [7, 27–31].

### Protocolized volume expansion at diagnosis of HUS might reduce the severity of the subsequent clinical course

Based on data suggesting that volume contraction at presentation with HUS is a risk factor for poor outcomes, Ardissino et al. developed a systematic approach to the management of newly presenting children with HUS. In a study of 76 children using a pre-post design and a “treat-to-target” approach with a goal of 10% body weight increase from baseline, these authors report that renal replacement therapy (RRT) use decreased from 58 to 26% [18]. A similarly designed study in Argentina demonstrated that 16 children consecutively presenting with HUS who received 27 mL/kg over a 3-h period had greater urine output and were less likely to require RRT than 19 historical controls who were fluid restricted upon admission.

### Pre-HUS volume expansion is associated with less severe episodes of HUS

In a prospective, single-center study of 29 children with HUS [20], those who developed anuria received less intravenous sodium and fluid volumes during the pre-HUS period. Similar findings emerged from in an 11-center prospective cohort study of 50 children with HUS [19]—those who received no intravenous fluids within 4 days of diarrhea onset (i.e., before they developed HUS) were 1.6 times more likely to develop oligoanuric renal failure.

Additional data from the diarrhea phase pre-HUS suggest the need for, and feasibility of, volume expansion early in illness, to reduce the severity of HUS. McKee et al. studied 866 children infected with STEC, who did not have HUS at initial presentation in a network of 38 North American pediatric emergency departments [16]. In regression analysis, the development of HUS was associated with higher initial hematocrit values and the delayed receipt of intravenous fluids.

A meta-analysis of eight studies and 1511 children [26] concluded that intravenous fluid administration up to and including the day of HUS diagnosis was associated with a reduced need for RRT [26]. Moreover, relative hemoconcentration was associated with the development of oligoanuric renal failure and death [26]. In addition, compared to euvolemic patients, clinically dehydrated patients at HUS diagnosis have an increased risk of death [26].

The feasibility of reducing the anuria rate was suggested in a study of 36 STEC-infected children who were admitted to hospital before they developed HUS [13], most of whom received aggressive parenteral volume expansion. Only 11 (31%) of these 36 patients experienced anuria, a rate much lower than that in other recent series, where typically 50 to 60% [16, 32–34] require RRT. This study complements observational data supporting the benefit of volume expansion in the pre-HUS phase [13, 19, 20, 35] and lends support to the hypothesis that RRT rates can be reduced.

These multiple lines of evidence suggest the potential benefits of intravascular volume expansion in STEC-infected children. However, the strength of the conclusions that can be drawn and the impact on clinical care are limited by heterogeneity of design, small numbers, lack of clear protocols, unmeasured confounders, and difficulty differentiating causality from association. Our proposed study aims to resolve this uncertainty by comparing protocolized management of hyperhydration versus conservative fluid management.

### Objectives {7}

Our *primary objective* is to determine whether children diagnosed with a high-risk STEC infection who receive early intravenous fluid administration targeting intravascular volume expansion (i.e., hyperhydration) experience better kidney outcomes as defined by major adverse kidney events within 30 days (MAKE30) compared to children treated with a conservative fluid management approach.

Our *secondary objectives* are to determine whether there are differences in (1) the frequency of life-threatening, extrarenal complications of HUS and (2) the proportion that develops HUS of any severity between participants allocated to receive hyperhydration, compared to those allocated to receive conservative fluid management.

Our *exploratory/tertiary objectives* are to further our understanding of the pathophysiology of HUS and identify predictors of HUS.

### Trial design {8}

This is a phase III, multinational, multicenter, embedded, cluster-randomized, crossover trial comparing hyperhydration versus conservative fluid management of children with high-risk STEC infections.

## Methods: participants, interventions, and outcomes

### Study setting {9}

Twenty-six tertiary care academic pediatric institutions located in the United States and Canada, and their patient catchment regions (Fig. 1).

**Fig. 1 Fig1:**
[figure not shown]
Location of 26 participating tertiary care academic pediatric institutions

### Eligibility criteria {10}

#### Screening criteria

Participating sites will establish a systematic process to identify all children with high-risk STEC infections within their institution’s catchment area. The process varies by site but includes the creation of electronic dashboards that identify all stool specimens that are positive for an STEC pathogen and the screening of all admission and discharge diagnoses. In addition, as many sites serve as referral institutions, any patient identified as likely having a high-risk STEC infection (defined below) within 24 h of result notification will be screened for eligibility. This time limit ensures that the participating site’s allocated treatment pathway can be initiated early in the disease course. Patients identified only because their condition deteriorated and were deemed to require transfer to a participating hospital for tertiary level care were ineligible as their inclusion would bias our study towards the null hypothesis as most such children will experience the primary outcome shortly after enrollment and would not have received the allocated pathway prior to transfer. Once screened and the clinical care pathway initiated, patients could be approached for study participation (which is limited to data and biospecimen collection as the clinical care pathways are embedded into routine care at study sites) up to 7 days following identification.

#### Inclusion criteria

Age 9 months to < 21 yearsShiga toxin 2 (Stx 2)-positive *E. coli* infection OR a history of bloody diarrhea and evidence of STEC infection OR a presumptive diagnosis of HUS in an individual with a history of diarrhea

#### Exclusion criteria

Presence of advanced HUS, defined by:Hematocrit < 30% ANDPlatelet count < 150 × 10^3^/mm^3^ ANDCreatinine > 2.0 mg/dL (177 µmol/L)i)The presence of only 1 or 2 of these criteria will not result in patient exclusion, regardless of how close the 3rd criterion is to meeting the exclusion criteria.Prior episode of HUS or diagnosis of atypical HUS [36]Chronic disease limiting fluid volumes administered (e.g., impaired kidney, liver, or cardiac function, chronic lung disease)Evidence of anuria (i.e., no urine output for > 24 h)Hypoxemia requiring oxygen therapyHypertensive emergency defined as:Elevated blood pressure above the 99th percentile for age [37]ANDEvidence of neurological change (any of the following)i)Seizureii)Diplopia or blurred visioniii)Severe vomitingiv)HemiplegiaORSevere chest pain with any of the below:i)Cardiomegaly on chest X-RAYii)Left ventricular hypertrophy on electrocardiogram or echocardiogramiii)Pleural effusions on X-ray

7)Greater than or equal to 10 days since onset of diarrhea or if no diarrhea then the onset of other symptoms [19]8)Known pregnancy9)Language barriers impairing appropriate conduct of the study protocol and/or inability to obtain informed consent

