#### End-of-fluid protocol criteria

The pathways will end when the at-risk window for developing HUS, or worsening HUS if present, has passed and this time point is defined by:Platelet count is > 50 × 10^9^/L (in the absence of transfusion) ANDPlatelets have increased by ≥ 5%* (in the absence of transfusion) since preceding test ANDAbsence of diarrhea (loose or watery stool) × 24 h AND ≥ 5 days since the onset of diarrhea

*If >10 days since the onset of diarrhea, up to a 5% decrease in platelet count since preceding test is acceptable.

In addition, the fluid pathways should no longer be followed in children meeting any of the following criteria:Decision to initiate RRTAnuria for ≥ 12 hHypoxemia requiring supplemental oxygenWeight gain > 15%Hypertensive emergency

If *any of* these criteria are met, the treatment pathway will not resume once they are resolved; care tailored to each patient should be provided as directed by the responsible physician.

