#### Secondary outcomes

These will focus on quantifying other measures of efficacy and safety. They have been selected to provide supportive information about the effect of volume expansion on the primary outcome and the natural history of disease (see Table 1).

**Table 1 Tab1:** Outcomes

Outcome measures			
Type	**Name**	**Time frame**	**Brief descriptions**
Primary	Major adverse kidney events to 30 days (MAKE30)	30 days	MAKE30 is defined as: 1) Death due to any cause censored at 30 days after enrollment OR 2) Provision of RRT, any modality, within 30 days of trial enrollment OR 3) Sustained loss of kidney function (100% increase of serum creatinine from baseline at 30 ± 7 days) Baseline serum creatinine: eGFR (120 ml/min/1.73m^2^) will be used to impute an estimated baseline value. This estimate will be applied to all patients as most patients will not have a baseline value from within the 3 months preceding study 30-day serum creatinine: these will only be required for participants with an elevated value at the time of fluid pathway termination who do not receive RRT

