### Sample size

#### Target study sample size

We estimate the overall study sample size required is 1040. The number to be screened will likely be 25% higher given that some children will be ineligible, and some will decline consent. Preliminary data indicate that the primary outcome event rate in the conservative fluid management arm will be approximately 10%. The study will be powered to detect a 5% absolute reduction (risk ratio 0.5) in the rate of MAKE30 in the hyperhydration arm. Using a conservative estimate of 5–15 subjects per year per site, we used simulated data (R software) to generate a power table (Table 3) for a 20- or 26-site cluster-crossover design under varying underlying intra-class correlation (ICC) values. The table shows that power is not highly dependent upon ICC and that 20 and 26 sites are required for 80% and 90% power, respectively, at the ICC estimated from preliminary data (i.e., 0.106) [16]. We expect very low levels of missing data, as participants with elevated creatinine values at the time of discharge will have laboratory follow-up as part of their standard clinical care. Patients who deteriorate and develop the MAKE30 outcome will be readily identified. Thus, the impact of loss to follow-up on power is expected to be minimal.

**Table 3 Tab3:** Power calculations for the primary outcome

Intraclass correlation coefficient	20 cites (approx. 800 subjects)	26 sites (approx. 1040 subjects)
0.05	82%	89%
0.106^a^	81%	90%
0.15	85%	94%

^a^Estimate from preliminary data [16]

The anticipated HUS rate in the conservative fluid management arm is 17.5%, and the rate of extrarenal complications is 7.5%. Detectable absolute differences for these two outcomes with 80% and 90% power, at approximately the same ICC as estimated for the primary outcome, are provided (Table 4). Here, a conservative Bonferroni correction (alpha = 0.025) is used.

**Table 4 Tab4:** Power calculations for secondary outcomes

Outcome	Power	Detectable difference with 20 sites (*n* = 800)	Detectable difference with 26 sites (*n* = 1040)
Hemolytic uremic syndrome—17.5% in conservative fluid management arm	80%	7.2%	6.3%
	90%	8.1%	7.1%
Extrarenal complications—7.5% in conservative fluid management arm	80%	4.7%	4.1%
	90%	5.2%	4.6%

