## Statistical methods

### Statistical methods for primary and secondary outcomes {20a}

Baseline characteristics of subjects will be summarized by intervention group. Counts and proportions will be used for categorical variables and means, standard deviations, medians, and quartiles will be used for numeric variables.

We will adhere to the ITT principle. The primary outcome, the MAKE30, will be compared between children allocated to hyperhydration vs. those allocated to conservative fluid management. We will use logistic regression with generalized estimating equation (GEE) methods to account for clustering at the site level. Fixed model terms will include treatment effect and period effect. Other baseline terms in the model will be age (as a continuous variable), serum creatinine, and hematocrit. These variables have been associated with adverse kidney outcomes in this population. The superiority test of null treatment effect will be carried out at the 0.05 level. Parameter estimates and 95% confidence intervals will be provided for all model terms. Carry-over effect will not be present in our crossover design in the traditional sense as patients themselves, and therefore, their outcomes will only be subject to one type of treatment. The only possible “carryover” effect would be a lack of adherence to the new treatment protocol after the crossover at the site level. We will monitor this closely and its potential effect which would be to reduce power.

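### RRT status at entry is left open: a few children whose RRT has started or been decided can be enrolled, and Table 1 counts that RRT as a primary event

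*Protocol article*

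**What the plan says.** All of this is in the protocol article.

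- **Inclusion criteria.** A presumptive HUS diagnosis with a history of diarrhea is enough to qualify.
- **Exclusion criteria.** Advanced HUS needs low hematocrit, low platelets and raised creatinine together: "The presence of only 1 or 2 of these criteria will not result in patient exclusion, regardless of how close the 3rd criterion is". Anuria beyond 24 h also excludes. None of the nine exclusions mentions RRT.
- **Screening criteria.** Children found only because they deteriorated and needed transfer are ineligible, because including them "would bias our study towards the null hypothesis as most such children will experience the primary outcome shortly after enrollment".
- **End-of-fluid protocol criteria.** "the fluid pathways should no longer be followed in children meeting any of the following criteria", and the list that follows includes a decision to initiate RRT.
- **Table 1, primary outcome.** The RRT component is "Provision of RRT, any modality, within 30 days of trial enrollment". The Abstract (Methods) and the section on statistical methods for primary and secondary outcomes instead limit it to newly initiated RRT.
- **Non-adherence and missing data.** The primary analysis keeps every enrolled participant in the arm assigned to the site.
- **Secondary outcomes.** Children with HUS at baseline are left out of the HUS analysis. No comparable step is described for MAKE30.

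**The concern.** If RRT is already running or already decided when a child enters, neither pathway can change that component of the outcome. Such a child adds an event whichever arm the site is in. Events of this kind move the risk ratio towards 1 and lower power. The protocol accepts this argument for deteriorated transfers, but its safeguard works by referral route and not by RRT status. The same child presenting directly to a participating hospital is not covered.

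The two definitions of the RRT component add a second problem. For RRT already under way at entry, one wording counts an event and the other does not, so adjudicators could classify the same child differently.

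**Working it through.** **Step 1: entry list against pathway-end list.** There are five additional conditions under which the pathway stops.

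| Pathway-end condition | Entry exclusion? |
|---|---|
| Hypoxemia needing oxygen | Yes |
| Hypertensive emergency | Yes |
| Anuria (12 h or more) | Yes, but at more than 24 h |
| Weight gain above 15% | Not applicable; arises on treatment |
| Decision to initiate RRT | No |

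The RRT decision is the only condition that can exist at presentation and has no entry counterpart.

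**Step 2: tracing a child through the text.** Take a child who presents directly with presumptive HUS, meets two of the three advanced-HUS criteria, has passed urine within 24 h and meets no other exclusion. That child is eligible.

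- RRT decided before time 0: the pathway should not be followed, and the RRT that follows is an event under both wordings.
- RRT started before time 0 and continuing: an event under Table 1, but not under the new-RRT wording.

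**Step 3: reproducing the stated power.** Inputs from the sample size section: 10% against 5%, 1040 children (520 per arm), 26 sites, ICC 0.106. The test level is from the statistical methods: "The superiority test of null treatment effect will be carried out at the 0.05 level". Two-sided testing is assumed, since sidedness is not stated there. With equal within-period and between-period correlation, the cluster-crossover design effect is 1 − ICC, so the effective size per arm is m = 520/0.894 = 581.7.

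Power = Φ{[d√m − 1.96√(2p̄(1−p̄))] / √(p₁(1−p₁)+p₂(1−p₂))}

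= Φ{[0.05 × √581.7 − 1.96√(2 × 0.075 × 0.925)] / √(0.09 + 0.0475)}

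= Φ{(1.206 − 0.730)/0.371} = Φ(1.283) = 90.0%.

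With 20 sites (m = 400/0.894 = 447.4) the result is 81%. Both agree with Table 3 at ICC 0.106. A simulated cluster-crossover with logistic GEE gave 88–91% and 79–82%. The planned figures therefore reproduce.

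**Step 4: adding a fixed share.** Let f be the share of enrolment whose RRT event is fixed at entry, with the planned rates holding in everyone else: p₁ = f + (1−f) × 0.10 and p₂ = f + (1−f) × 0.05. The documents do not give f; the values below are assumptions.

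| f | Children of 1040 | p₁ v p₂ | Difference (points) | Risk ratio | Power |
|---|---|---|---|---|---|
| 0 | 0 | 10.00% v 5.00% | 5.00 | 0.50 | 90.0% |
| 0.5% | about 5 | 10.45% v 5.48% | 4.98 | 0.52 | 88.1% |
| 1% | about 10 | 10.90% v 5.95% | 4.95 | 0.55 | 86.1% |
| 2% | about 21 | 11.80% v 6.90% | 4.90 | 0.58 | 82.0% |

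**Step 5: the less favourable assumption.** If these children are already inside the 10% control rate and only the remaining events are halved, p₁ = 0.10 and p₂ = f + (0.10 − f)/2. For f of 0.5%, 1% and 2%, p₂ is 5.25%, 5.50% and 6.00%, and power is 86.4%, 81.9% and 71.1%. The documents do not say which assumption applies. The cohort cited for the ICC consisted of children without HUS at first presentation. If the 10% rate came from the same cohort, adding on top is the more natural reading, but the source of the 10% is described only as preliminary data.

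**The case against.** Much can be said against a strong form of this point, and most of it stands.

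- **The group is narrow.** Children meeting all three laboratory criteria, those with anuria beyond 24 h, those on oxygen, those with hypertensive emergency, those 10 or more days from onset and deteriorated transfers are already out. No document gives a frequency for the remainder.
- **Already met is not settled.** On the new-RRT wording, RRT started before entry is no event. Only Table 1's wording makes it one. RRT that is decided but not started escapes this objection.
- **The entry flow closes part of the gap.** The Screening criteria describe approaching families after screening and pathway initiation, so a child for whom the pathway never began may not be approached. The consent section weakens this: the research team is alerted whatever clinical decision was made.
- **The absolute difference hardly moves.** It goes from 5.00 to 4.90 points at f = 2%. The power loss comes mainly from higher event rates in both arms.

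A reader might go further and infer that the all-three rule for advanced HUS is itself faulty, because it admits hemoconcentrated children and the background reports that those with "hemoconcentration and/or dehydration at admission (i.e., when HUS is diagnosed) have worse outcomes". The documents do not support that. The rule is an explicit, deliberate bright line. The background also gives reasons to treat such children, including a pre-post study in which RRT use fell from 58% to 26% with volume expansion at HUS diagnosis. Poor prognosis is not an outcome fixed at entry.

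**Conclusion.** The gap is real but small. The entry criteria are silent on RRT started or decided before time 0, the pathway-end criteria are not, and the outcome definitions disagree on whether RRT must be new. The protocol itself supplies the direction of the effect, towards the null.

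The size is conditional. With 0.5% to 2% of enrolment added on top of the planned rates, power falls from 90% to between about 88% and 82%. This rests on an assumed share, on treating an RRT decision as certain to lead to RRT, on two-sided testing and on a design effect of 1 − ICC. If the share is zero, the stated 90% stands; the sample size calculation contains no error on this account.

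A reader might infer that many enrolled children will already have the primary outcome at entry, or that the trial is underpowered. The text shows only that such entries are possible.

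**What to change.** 1. Reconcile the Screening criteria, Exclusion criteria, End-of-fluid protocol criteria, Table 1 and the statistical methods on RRT status at time 0.
2. Exclude children whose RRT was initiated before time 0, judged by a recorded time stamp and applied identically in both arms.
3. Define the MAKE30 component everywhere as new RRT initiated after time 0.
4. Add a sensitivity analysis of MAKE30 without children whose documented RRT decision predates time 0, reporting the number removed by arm.

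The cost is one eligibility line, one time field, one wording change and one extra analysis, with a few fewer children enrolled.

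Item 4 should remain a sensitivity analysis. When RRT is decided is a clinician's judgement, the trial is unblinded and each site knows its allocation before a child presents. A filter on decision time could therefore select differently by arm and replace non-differential dilution with selection bias. The start of RRT is a more objective event, which is why the exclusion in item 2 is tied to it.
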